### Outcome variables

#### Outcomes

Our primary outcomes will be clinical measures captured in the VA electronic health record, including BMI (constructed from height and weight values) and blood pressure readings (systolic and diastolic), which will be obtained from the Vital Status table in the VA Corporate Data Warehouse (CDW). In addition, HbA1c will be obtained from CDW laboratory data. A power analysis revealed that our planned sample will result in minimal detectable differences for HbA1c of 0.6 mmol/mol, for systolic blood pressure of 6.5 mm and 3.5 Hg for diastolic blood pressure, and 2.4 in BMI units (weight pounds x height inches) × 703).

We will construct healthcare cost variables from VA Managerial Cost Accounting datasets, which is an activity-based cost accounting system that maps VHA resource expenditures to individual patient encounters. Healthcare costs will be captured separately for outpatient, inpatient, emergency department, and pharmacy services. We will sum these costs for healthcare encounters occurring over the follow-up period and adjust for inflation to 2025 US dollars. Similarly, healthcare utilization will be calculated as the number of outpatient and emergency department visits, prescriptions, and inpatient days. These will serve as important secondary outcomes.

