### Data analysis

At baseline, descriptive analyses of participants and the comparison group will assess any group differences in their characteristics (implementation or comparison), diet-sensitive condition, location site, age, military branch, and race/ethnicity. The index date for the treatment group will be the date of enrollment in the VA FCPRx program, while the index date for the comparison group will be the first date during our enrollment window in which the Veteran was listed on the eligibility roster and screened positive for food insecurity. We will construct propensity scores for program enrollment using multivariable logistic models including the independent variables listed above and use these propensity scores to conduct inverse probability treatment weighting (IPTW) analyses to compare outcomes between individuals in the FCPRx group and the comparison group. For each of these variables, our primary measure will be the value most proximal within a 2-month window surrounding the follow-up time period (i.e., 6 and 12 months). In secondary analyses, we will calculate averages for individuals with multiple values. In addition, our primary analyses will carry forward baseline values for individuals with missing values in the follow-up period. In exploratory analyses, we will include only those with non-missing outcome values.

In our primary analysis, we will assess differences in clinical measures, including body mass index (BMI), systolic blood pressure (SBP), diastolic BP (DBP), A1c, and self-reported health between patients in the treatment and comparison groups. For each outcome of interest, we will use a linear model with an ITPW approach to estimate the treatment effect and ensure the balance of baseline covariates, including baseline clinical measures. As a secondary analysis, we will compare within-person changes in clinical measures between the two groups.

Secondary outcomes include healthcare cost and utilization, and self-rated health. Exploratory outcomes include fruit and vegetable consumption, nutrition security, depression symptoms, and well-being indices. We will assess changes in secondary and exploratory outcome measures for those participants with both baseline and follow-up values. We will use generalized linear models and two-part models for healthcare cost outcomes and Poisson or negative binomial models for healthcare utilization outcomes. All comparisons will be performed at both 6- and 12-month follow-up intervals.

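### Cost and utilization are described both as changes from baseline and as follow-up totals, so the secondary contrast is not uniquely defined; the readings can diverge if a pre-index gap in use survives weighting

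*Protocol article*

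**What the plan says.** All references are to the Methods of the protocol article.

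- **Which outcomes are secondary** (Data analysis): "Secondary outcomes include healthcare cost and utilization, and self-rated health".
- **How secondary outcomes are assessed** (Data analysis, shortly after): "We will assess changes in secondary and exploratory outcome measures for those participants with both baseline and follow-up values". Cost and utilization are not exempted.
- **Which models are used** (Data analysis, next sentence): "We will use generalized linear models and two-part models for healthcare cost outcomes and Poisson or negative binomial models for healthcare utilization outcomes".
- **How cost is built** (Outcomes): "We will sum these costs for healthcare encounters occurring over the follow-up period and adjust for inflation to 2025 US dollars".
- **How utilization is built** (Outcomes, introduced as parallel to cost): "healthcare utilization will be calculated as the number of outpatient and emergency department visits, prescriptions, and inpatient days".
- **When** (Data analysis): "All comparisons will be performed at both 6- and 12-month follow-up intervals".

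For the clinical measures, the Data analysis section does rank the two contrasts. The weighted comparison of follow-up values is primary, and within-person change is a secondary analysis. No such ranking is given for cost and utilization.

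**The concern.** The sentence on changes needs a baseline value of cost and use. The visible text states no pre-index window from which to build one. The variable definitions and the assigned models point to a follow-up total instead. An analyst could follow either sentence and be within the plan.

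This matters because the groups are not randomized. The comparison group consists of eligible Veterans who were not offered the program or declined it, and the Limitations section expects confounding to affect the estimates. A contrast of totals carries any remaining difference in prior use into the result. A contrast of changes removes a stable difference but is a different quantity. The article presents evidence on healthcare costs as one of its main products, so the choice should be settled before results are seen.

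**Working it through.** The plan states no effect size, power or variance for cost or utilization, so there is no figure of its own to reproduce. Three checks were made.

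**1. Do the assigned models fit a subtracted score?** Models were fitted to a small set of differences that included negative values.

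- Poisson: no estimates.
- Negative binomial: fit failed.
- Gamma with log link: fit failed.
- Gaussian with identity link: fitted.

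The count models and the usual skewed-cost models therefore cannot take a difference score; a Gaussian generalized linear model can. The count models can still estimate change if each Veteran contributes a pre-index and a post-index record and the model has a group-by-period term.

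**2. When do the two readings disagree?** Let B be the mean before the index date and F the mean after it, with subscript 1 for the program and 0 for comparison.

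- Total reading: F₁/F₀.
- Change, additive: (F₁ − B₁) − (F₀ − B₀).
- Change, ratio scale: (F₁/B₁)/(F₀/B₀).

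Inputs: 500 in the program group (the article's enrollment target). Everything else is assumed: 500 in the comparison group, gamma-Poisson counts with variance parameter 1, the visit means below, and no weighting. There were 300 runs per row, tested at two-sided 5% with robust standard errors. Expected values follow from the formulas; percentages are shares of simulated runs.

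| Mean visits before (program v comparison) | After | Total ratio | Additive change | Ratio of ratios |
|---|---|---|---|---|
| 6 v 6 | 5.4 v 6 | 5.4/6 = 0.90; significantly lower in 34% | −0.6 − 0 = −0.60; lower in 78% | 0.90; lower in 81% |
| 6.6 v 6 | 5.94 v 6 | 5.94/6 = 0.99; significant in 2% (higher) and 3% (lower) | −0.66 − 0 = −0.66; lower in 86% | 0.90; lower in 84% |
| 8 v 6 | 7.2 v 6 | 7.2/6 = 1.20; significantly higher in 74% | −0.8 − 0 = −0.80; lower in 93% | 0.90; lower in 86% |
| 4 v 2 | 5.4 v 3 | 5.4/3 = 1.80; higher in 100% | 1.4 − 1.0 = +0.40; higher in 57% | 1.35/1.50 = 0.90; lower in 53% |

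With balanced baselines (row 1) the readings agree in direction. With a 10% gap (row 2) one is null and the other significant. With a 33% gap (8/6 = 1.33, row 3) both were significant in opposite directions in 68% of runs. Row 4 shows that change itself depends on the scale.

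**3. What if the program does nothing?** This is a second simulation with assumed inputs: 2,000 trials per setting, 500 per group, mean 8 visits, gamma patient heterogeneity plus period-to-period noise, unweighted. Any gap applies equally before and after the index date. The total was tested by a rate ratio with robust variance, and the change by a Welch t-test. Rejection rates:

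| Setting | Total | Change |
|---|---|---|
| No gap, no effect | 5% | 6% |
| 10% gap, no effect | 22% | 5% |
| 20% gap, no effect | 58% | 5% |
| 20% gap, true rate ratio 0.83 | 5% | 66% |

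In the last row the gap and the effect cancel in the total (1.2 × 0.83 ≈ 1.00). About 43% of individual changes were negative.

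**Is a remaining gap plausible?** The Independent variables section names demographic characteristics, the Charlson index and mental health diagnoses. The Data analysis section adds baseline clinical measures. Prior cost and prior use are not named. Table 2, to which the article refers for further measures and analytic approach, is not visible.

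**The case against.** The best defence is that the sentences can be read together. A rule requiring both a baseline and a follow-up value fits the surveys, which are given at enrollment, 6 and 12 months with non-response expected. It covers self-rated health and all the exploratory outcomes. The next sentence then gives cost and utilization their own models, which match totals and counts. That is a natural reading and may well be the intended one. It is not what the sentence says, however, and the remedy is to say it.

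Several stronger inferences are tempting, and the documents do not support them.

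- **That the named models cannot estimate change.** This is true only of a subtracted score for the count and skewed-cost models. A group-by-period term works in the same models, a Gaussian model accepts a difference, and the article never says that costs or counts will be subtracted.
- **That no baseline cost or use exists.** The article states no pre-index window, but the same VA datasets can supply one. The full protocol or Table 2 may define it.
- **That zero users will be dropped.** Zero cost or zero visits is a value, and naming a two-part model suggests that zeros are kept.
- **That the two readings will generally reverse.** Reversal needed an assumed 33% gap left after weighting. The no-effect simulation shows significant against non-significant results, not opposite signs.

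It is also fair to say that the 58% rejection rate measures residual confounding, which the Limitations section already discloses. Letting the gap be the same before and after is the condition most favourable to the change contrast.

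**Conclusion.** The point holds in a limited form. Taken at its word, the Data analysis section assesses cost and utilization as changes, while the variable definitions and assigned models describe follow-up totals. The contrast is not uniquely defined, which is less than saying that it is undefined.

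The consequence is conditional. If pre-index use is balanced after weighting, the two readings agree in direction. If a gap of 10% to 20% remains and the program has no effect, the total was significant in 22% to 58% of simulated trials, against 5% for the change. These rates rest on assumed visit means, dispersion and gaps, an assumed comparison group of 500, and no weighting. They show sensitivity and do not predict this study's error rate.

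Only secondary outcomes are affected. The repair is still worth making, because it settles the contrast and also closes a likely route for bias in a non-randomized comparison.

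**What to change.** In Data analysis:

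1. Limit the sentence on changes in those with both values to survey-reported outcomes.
2. For cost and utilization, state that the response is the total from index to month 6 and from index to month 12, in all Veterans including those with zero use. Analyse it with the propensity-weighted two-part model (cost) or count model (utilization).
3. Include the same variable, summed over an equal-length period before the index date, in the propensity model or the outcome model.
4. If change is the intended contrast, estimate it with a group-by-period term in these models and name the scale (ratio or difference).

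Item 3 goes beyond reconciling the sentences: it is an added adjustment, justified by the non-randomized design. The cost is one rewritten paragraph and one extra pull of pre-index cost and use from the same VA datasets. No new data collection from Veterans is needed.

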**Methods:**

This pragmatic, quasi-experimental intervention study of effectiveness and implementation of a produce-prescription program is conducted in 2 VA hospital health systems in Salt Lake City, Utah, and Houston, Texas. Eligible Veterans have (a) a diet-sensitive cardiometabolic health condition (obesity, hypertension, and/or diabetes) identified in the electronic health record (EHR) by diagnostic codes (ICD-10) and/or lab values and (b) low-income identified by priority status in administrative data. Program enrollment is pragmatically integrated within the VA clinical care process of food security screening and service referrals. Eligible Veterans who screen positive for food insecurity during clinical care processes are referred to the intervention. The Veterans Affairs FreshConnect Produce Prescription (VA FCPRx) intervention program includes 12 months of a produce prescription allowance for purchasing fresh fruits or vegetables, provided as $100 monthly on a pre-paid card for use at local grocery stores. The program also includes culinary education through cooking courses provided by VA nutritionists or nutritional consults provided one-on-one by a VA dietitian. Process and outcome measures will be evaluated using the PRISM RE-AIM framework. Health outcomes related to diet-sensitive chronic conditions (e.g., HbA1c levels for patients with diabetes) and healthcare costs (e.g., outpatient costs) are assessed using EHR data. VA FCPRx participant outcomes are assessed in comparison to a group of similar Veterans using intention-to-treat analyses. Patient-reported outcomes, implementation strategies and outcomes, and staff and Veteran experience are assessed with a combination of surveys, focus groups, and program administrative data.

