## Methods

### Study design

Veterans experiencing or at risk for food insecurity, diagnosed with a cardiometabolic diet sensitive condition including hypertension, obesity, and/or diabetes, and a comparison group of similar Veterans will be enrolled in VA FCPRx to estimate the effect of produce prescription on clinical measures, healthcare utilization, and self-reported behavior and well-being.

Primary outcomes: Clinical measures, including body mass index (BMI), blood pressure, and metabolic control (HbA1c) derived from the VA EHR.

Secondary outcomes: Healthcare utilization, including primary care visits, pharmacy utilization, inpatient admissions, and ED visits. Veteran-reported health outcomes, including subjective ratings of health.

Exploratory outcomes: Veteran-reported consumption of fruits and vegetables, nutrition security, depression symptoms, and other well-being indices.

We will also assess implementation processes and outcomes.

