### Eligibility and screening

Eligible participants are identified using VA EHR data from among currently active patients defined by a visit to a participating VA medical center within the preceding 12 months. Inclusion criteria are:

1) An indicator in the VA EHR for economic hardship (Designated membership in VA benefits criteria priority groups 5 or 7, based on Veteran benefits. These groups indicate a Veteran who has low-income without a service-connected disability).

2) One or more diet-sensitive cardiometabolic condition a) hypertension, b) obesity, or c) type 2 diabetes or malnutrition related diabetes. Cardiometabolic condition is determined by diagnostic code within the VA EHR (International Classification of Disease, ICD-10) or by laboratory values. Table 1 shows the specific EHR ICD-10 codes and laboratory values. Consent is not required for this screening or identification process.

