We will use an approach in which we will assign participants to the VA FCPRx group if they enrolled in the VA FCPRx program regardless of whether or how much of the monetary and nutrition education benefit they used over the 12-month follow-up period. In exploratory analyses, we will use a sub-analysis approach to compare enrolled patients by outcomes based on the amount of financial and educational benefit used.

Our primary analyses will consider all enrolled patients in the VA PRx group. In subgroup analyses, we will break the VA PRx patients into mutually exclusive categories based on the amount of produce purchased and adherence to the educational component of the program. For financial benefit, we will compare participants who used their card minimally, moderately, and fully. These categories will be derived based on the distribution of card use in the sample. For the educational benefit, we will compare participants who did not attend culinary education classes at all, to those who participated some of the time, to those who participated in all 4 classes. We will assess comparison group participants by reasons for non-enrollment, including not being approached for enrollment or declining to enroll. Results of these sub-analyses will inform discussions of potential selection biases and the impact on results. We may perform additional subgroup analysis, including by VHA site and other demographic differences such as race or ethnicity. Qualitative data (e.g., interview transcripts) will be analyzed using approaches including thematic analysis by an experienced qualitative team [68].

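### The primary HbA1c comparison runs over the whole treatment and comparison groups, although entry does not require diabetes and the Abstract describes HbA1c for patients with diabetes

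*Protocol article*

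**What the plan says.** The Study design section names as primary outcomes "Clinical measures, including body mass index (BMI), blood pressure, and metabolic control (HbA1c) derived from the VA EHR". Under Eligibility and screening, the clinical entry criterion is "One or more diet-sensitive cardiometabolic condition a) hypertension, b) obesity, or c) type 2 diabetes or malnutrition related diabetes", so a Veteran with hypertension alone or obesity alone qualifies.

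The Data analysis section assesses differences in BMI, systolic and diastolic pressure and HbA1c "between patients in the treatment and comparison groups". It attaches no condition to any of them. Later it says "Our primary analyses will consider all enrolled patients in the VA PRx group", following a paragraph that assigns Veterans to the program group "regardless of whether or how much of the monetary and nutrition education benefit they used over the 12-month follow-up period". The planned subgroups are by benefit use, reason for non-enrollment and possibly site and demographics. The qualifying condition is not among them.

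The Methods part of the Abstract reads differently: "Health outcomes related to diet-sensitive chronic conditions (e.g., HbA1c levels for patients with diabetes".

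On data, the Outcomes section says "HbA1c will be obtained from CDW laboratory data", and no study-ordered test is described. The primary value is the one closest to 6 or 12 months within a 2-month window. A missing follow-up value is replaced by the baseline value in the primary analysis. The weighted model is meant to balance baseline clinical measures as well.

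**The concern.** The article gives two different populations for one primary outcome. Under the Abstract, HbA1c is assessed in Veterans with diabetes. Under Data analysis, it is compared across everyone, including Veterans who entered on blood pressure or weight alone.

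The choice changes the quantity estimated. If the program lowers HbA1c mainly in diabetes, the whole-group difference is roughly the share with diabetes times the effect in diabetes. A null or small result would then be hard to read, since it could reflect either a weak program or a low diabetes share.

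There is also a data problem. A Veteran with a baseline but no follow-up HbA1c contributes zero change by construction. A Veteran with no HbA1c at all has nothing to carry forward and no observed baseline to balance on. HbA1c comes only from laboratory records, so this can happen, and it is more of an issue in a population not selected for diabetes.

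**Working it through.** **1. The plan's own figure.** The Outcomes section gives a detectable HbA1c difference of 0.6, with the unit printed as mmol/mol. It states no SD, alpha, power, comparison-group size or n per outcome, so the figure cannot be reproduced. It can be inverted. With two-sided alpha 0.05 and 80% power (both assumed), detectable difference = (1.96 + 0.84) × SD × √(2/n).

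| n per group | Difference / SD | SD implied by 0.6 |
|---|---|---|
| 500 | 0.177 | 3.39 |
| 250 | 0.251 | 2.39 |
| 125 | 0.354 | 1.69 |

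The figure may rest on fewer than 500 per group. The article does not say whether any smaller set is a condition subset, a site or an effective sample size. The power statement therefore does not settle which population was intended.

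**2. Inputs for the illustration.** 500 in the program group is the stated minimum. 500 in the comparison group is assumed from the anticipated survey total of 1000. The rest are assumptions: SD 1.7 points with diabetes and 0.4 without, a mean gap of 1.6 points between them, a true effect of 0.6 percentage points in diabetes and none otherwise, and a diabetes share p of 30% to 60%. Variance inflation from weighting is ignored throughout.

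**3. Formulas.** Power = Φ(effect / (SD × √(2/n)) − 1.96).
- Whole group: effect 0.6p, n = 500.
- SD with no baseline adjustment: √(p·1.7² + (1−p)·0.4² + p(1−p)·1.6²).
- SD with the mean gap fully adjusted away: √(p·1.7² + (1−p)·0.4²).
- Diabetes only: effect 0.6, SD 1.7, n = 500p.

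**4. Worked case, p = 0.30.**
- The whole-group effect is 0.30 × 0.6 = 0.18.
- Unadjusted: SD = √(0.867 + 0.112 + 0.538) = 1.23; SE = 0.0779; ratio 2.31; power 64%.
- Adjusted: SD = √(0.867 + 0.112) = 0.99; SE = 0.0626; ratio 2.88; power 82%.
- Diabetes only, 150 per group: SE = 1.7 × √(2/150) = 0.196; ratio 3.06; power 86%.

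| Share with diabetes | Whole-group effect | Power, unadjusted | Power, gap adjusted | Power, diabetes only |
|---|---|---|---|---|
| 30% | 0.18 | 64% | 82% | 86% |
| 40% | 0.24 | 79% | 92% | 94% |
| 60% | 0.36 | 96% | 99% | 99% |

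**5. Direction.** With no effect outside diabetes, the ratio of the whole-group to the restricted signal is at most √p·1.7 / √(p·1.7² + (1−p)·0.4²). That is below 1 for any p under 1. The estimate itself shrinks to p times the effect in diabetes, whatever the adjustment.

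**6. Balance.** The primary contrast is on follow-up values, with within-person change secondary. A residual 10-percentage-point imbalance in diabetes share would shift the whole-group HbA1c contrast by 0.10 × 1.6 = 0.16 points, about the size of the diluted effect at p = 0.30. The Independent variables section names neither the qualifying condition nor baseline HbA1c, although it points to Table 2 (not shown) and Data analysis promises balance on baseline clinical measures.

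**The case against.** **The all-enrolled sentence is about benefit use.** This stands. It is an intention-to-treat rule and cannot by itself show that Veterans without diabetes enter the HbA1c contrast. The point rests instead on the outcome comparison in Data analysis, which carries no condition restriction, and on its conflict with the Abstract.

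**The detail may be in Table 2 or an analysis plan, neither of which is shown.** That is possible. It would explain a missing denominator, but not two visible statements that point to different populations.

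**Much of the power loss depends on ignoring baseline.** This also stands. Once the mean gap is adjusted away, the deficit at a 30% share falls from 22 percentage points to 4. The change in the estimand remains.

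**The average effect in all enrollees is a legitimate pragmatic estimand.** It is, and it should still be reported. For BMI, and less clearly for blood pressure, limiting the analysis to those with the condition is mainly a choice of estimand, and zero effect outside the condition is least plausible for BMI.

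**The missing-data section offers imputation of covariates and weighting for missing outcomes.** These could bring in Veterans with no HbA1c, but only by modelling a value or by letting others stand in for them. Data analysis names carry-forward as the primary approach.

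A reader might also infer three stronger claims that the documents do not support:
- *HbA1c is unmeasured in many enrollees.* No testing rate or condition mix is given.
- *Sparse testing without diabetes lowers whole-group power.* In the unadjusted model above it does the reverse. If only half of those without diabetes are tested, the diabetes share among tested Veterans rises from 30% to 46% and power from 64% to 69%. With a quarter tested, power is 75%.
- *Malnutrition-related diabetes makes the pooled BMI mean mix opposite directions.* No share or expected direction is stated.

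**Conclusion.** The concern holds for HbA1c. The Abstract and the Data analysis section describe different populations for a primary outcome and must be reconciled. The whole-group version reduces the HbA1c estimate to the diabetes share times the effect in diabetes, if other Veterans show no effect. It also includes Veterans who may have no value to carry forward or balance on.

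The power gain from restricting to diabetes is modest to substantial, depending on adjustment: 4 to 22 percentage points at a 30% share and at most about 3 at 60%. These figures are illustrative, because the SDs, the effect, the diabetes share and the comparison-group size are all assumed. For blood pressure and BMI, the conclusion goes no further than adding condition-specific contrasts.

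**What to change.** Reconcile the Abstract with the Data analysis section:
- Define the primary HbA1c population as Veterans in both groups who meet the Table 1 diabetes definition at the index date, keeping all such enrollees regardless of benefit use. The condition precedes exposure, so the intention-to-treat approach is kept.
- Check weight balance within that set, including baseline HbA1c.
- Restate n and the detectable difference for that set, with SD, alpha and power, and check the printed HbA1c unit.
- Report the all-enrollee HbA1c contrast as secondary, with the number in each group who have no HbA1c value.
- For blood pressure (hypertension) and BMI (obesity), report condition-specific contrasts alongside the all-enrollee ones.

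The cost is mostly wording, since eligibility screening already uses the diagnostic codes and laboratory values. The real downside is a smaller n for HbA1c, for example 150 per group at a 30% share, so the weights must perform in a smaller sample.

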### Intervention enrollment process (Screening)

Veterans who meet eligibility criteria are identified by a monthly VA EHR review by the evaluation team. Intervention enrollment will total at least 500 (250 per site). Enrollment will be closed once enrollment targets are reached. This was derived based on a power analysis performed on the primary outcomes coupled with practical considerations relating to the largest number of Veterans for whom the intervention and supportive health services would be available (see outcomes variables section for power analysis information). Of note, a recent systematic review of produce prescription programs included studies with adult sample sizes ranging from 21–243, thus, our planned sample of 500 is relatively large for the field to date [36]. Enrollment in the intervention group will continue until the planned sample size (*n* = 500) is reached.

A roster of eligible participants is made available on a secure Microsoft SharePoint site. This site is accessible only to the evaluation team and authorized nutritionists, dietitians, and social workers providing care to food-insecure Veterans. This screening approach supports the pragmatic enrollment process in this study. A Veteran who screens positive for food insecurity during clinical care is then referred to a social worker or dietitian. Social workers and dietitians at each study site are instructed to review the roster and offer FCPRx to Veterans who qualify (see Fig. 1). Veterans sign a release of information to permit information sharing with the Produce Prescription team. Figure 1 shows the study selection flow.

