#### Culinary education

Along with the monetary benefit of the program, participants will receive education designed to help them integrate the purchased produce into their diet, with a participant choice of: (1) a supportive nutrition class delivered in VA called Healthy Teaching Kitchen, offered virtually once per week for 4 weeks or (2) one-on-one consultation with a VA dietitian.

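### The education-adherence categories count only class attendance, although the component may be met by a dietitian consultation, so consultation-only Veterans are graded with non-users in an exploratory sub-analysis

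*Protocol article*

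**What the plan says.** The Culinary education section of the protocol article gives participants a choice: the Healthy Teaching Kitchen class, held virtually once a week for four weeks, or "one-on-one consultation with a VA dietitian". The Methods paragraph of the abstract describes the same two routes: "culinary education through cooking courses provided by VA nutritionists or nutritional consults provided one-on-one by a VA dietitian". Either one delivers the component.

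The Data analysis section plans to split enrollees into "mutually exclusive categories based on the amount of produce purchased and adherence to the educational component of the program". For education it defines three levels. The lowest and middle ones are given as follows: "we will compare participants who did not attend culinary education classes at all, to those who participated some of the time". The third and highest level is attendance at every one of the four sessions. The consultation is not mentioned there, and the comparison is not restricted to Veterans who chose the class.

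The same section gives the status of this work: "In exploratory analyses, we will use a sub-analysis approach to compare enrolled patients by outcomes based on the amount of financial and educational benefit used". The main comparison places every enrollee in the program group, whatever benefit was used.

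**The concern.** The stated construct is adherence to the whole educational component, but the rule measures only one of its two forms. A Veteran who chose the consultation and completed it did what the program asked, yet attended no class, and so shares a level with Veterans who took up neither option.

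Two things are at stake, both within the exploratory analysis. First, the reference group for class attendance is no longer a group without education, so the contrast cannot be read as education against none. Second, the article says these sub-analyses will inform its discussion of selection bias. Choice of option is the Veteran's own, so putting consultation users in the lowest level also mixes preference for a format with failure to engage.

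**Working it through.** The article gives no figure to reproduce. The main check is textual; the arithmetic only illustrates scale.

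**Step 1: place a consultation-only Veteran in the stated levels.**
- Literal reading: zero classes attended, so the lowest level.
- Stretched reading, with a consultation counted as partial participation: the middle level. The top level requires all four classes, so a completed consultation can never be graded as full adherence.
- Restricted reading, with levels applied only to class choosers: no level at all, and the text states no such restriction.

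None of the three gives this option a suitable level.

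**Step 2: share of the zero-class group that had a consultation.** Let u be the share of all enrollees who used neither option and c the share of education users who took the consultation only. Both are assumptions. Consultation-only Veterans are c(1−u) of enrollees, and the zero-class group is c(1−u) + u, so

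share = c(1−u) / [c(1−u) + u].

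**Step 3: contrast retained.** Let r be the consultation's effect relative to that of the class (assumed). With no confounding, the class-versus-zero contrast keeps the fraction 1 − r × share of its size.

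| c | u | Share with consultation | Kept, r = 1 | Kept, r = 0.5 |
|---|---|---|---|---|
| 0.10 | 0.50 | 0.05/0.55 = 9% | 91% | 95% |
| 0.25 | 0.50 | 0.125/0.625 = 20% | 80% | 90% |
| 0.25 | 0.20 | 0.20/0.40 = 50% | 50% | 75% |
| 0.50 | 0.20 | 0.40/0.60 = 67% | 33% | 67% |
| 0.50 | 0.10 | 0.45/0.55 = 82% | 18% | 59% |
| 0.75 | 0.10 | 0.675/0.775 = 87% | 13% | 56% |

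In numbers, at the planned 500 enrollees with c = 0.25 and u = 0.20, the zero-class group has 200 Veterans, of whom 100 had a consultation.

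**Step 4: when are consultation recipients a minority of that group?** The share falls below one half once u exceeds c/(1+c): 20% non-use at c = 0.25 and 33% at c = 0.50. Moderate non-use is enough.

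**Step 5: after re-cutting.** With consultation-only Veterans in their own category, the lowest level holds only those who used neither option, and the share is 0 whatever c and u are.

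**The case against.** The article never says in words that consultation users are coded as non-attenders. The sentence could be meant for class choosers only, since attending all four classes can apply to nobody else. Table 2, which is said to outline metrics and analytic approach, is not shown, nor is any analysis plan, and coding rules for exploratory subgroups often sit there. These points lower certainty about how the data will in fact be coded. They do not remove the mismatch: the levels are introduced as adherence to the component as a whole, no restriction is stated, and the published rule would need reconciling with the intervention description whatever those documents contain.

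A reader might infer more than the documents support:
- *That the lowest group would mostly consist of educated Veterans.* This needs low non-use. The Limitations section notes that no study resources were assigned to culinary education, so higher non-use is plausible, and at c = 0.25 and u = 0.50 the share is only 20%.
- *That the effect of education would necessarily be understated.* This holds if consultation works in the same direction as the class and selection is ignored. Attendance and choice of option are both self-selected, so the net direction of bias cannot be settled from the article.
- *That adherence to the program would be misreported.* The sentence sets groups for comparing outcomes; adherence reporting may be defined elsewhere.
- *That the main results are at risk.* They are not, because enrollees are counted whatever benefit they used.

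**Conclusion.** The point holds, at minor severity. The article offers two ways to meet the educational component and grades adherence by one of them. As written, consultation-only Veterans are placed with non-users, and no alternative reading gives them a fitting level. That conclusion rests on the text, plus the modest assumption that some Veterans take up the consultation.

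The size is open. Consultation recipients could be roughly 10–85% of the zero-class group across the assumed uptake and non-use shown. Shrinkage of the contrast further assumes a benefit in the same direction and no confounding by choice. Only the exploratory education sub-analysis is affected; the primary and secondary treatment-versus-comparison estimates stand.

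**What to change.** Replace the education levels in the Data analysis section with mutually exclusive categories that cover both options:
- neither option used;
- consultation only;
- 1–3 classes, with or without a consultation;
- all 4 classes, with or without a consultation.

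An equivalent choice is to grade completion of the option each Veteran selected and enter the option as a factor. Either way, reserve the label for no education for Veterans who used neither.

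State which dietitian contacts count. The enrollment sections have dietitians also reviewing the roster, offering the program and enrolling Veterans through the record template, so a rule based on any dietitian contact would create a new misclassification. Count only contacts recorded as nutrition education consultations.

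The cost is a short change of wording, one more and smaller category, and some data work to identify the consultations. It is best settled before outcomes are analyzed.
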